### 2.7. Inclusion Criteria

The inclusion criteria are:Accepted study participation (e.g., did not opt out);Female sex;Invasive BC;Negative preoperative assessment of the axilla, clinically and by ultrasound;Scheduled for primary surgery.

### 2.8. Exclusion Criteria

The exclusion criteria are:Did not accept study inclusion (i.e., opted out);Male sex;Children and adolescents (age < 18 years);Previous ipsilateral breast/axillary surgery;Synchronous distant metastases at diagnosis;Previous primary neoadjuvant therapy;Preoperatively verified axillary lymph node metastases by cytology or histology;Positive preoperative assessment of the axilla, clinically and by ultrasound;No surgical axillary staging;Upfront axillary nodal dissection.

### 2.9. Endpoints

#### 2.9.1. Primary Endpoint

The primary endpoint is defined as an axillary nodal status (discrimination, N0 vs. N+) determined from preoperative clinicopathological data from mammograms and core needle biopsies compared to a predictive N status by the algorithm.

#### 2.9.2. Secondary Endpoint

The secondary endpoint is defined as a false-negative rate of a maximum of 10% for the prediction of N0 vs. N+ compared to the histopathological assessment of excised sentinel lymph node(s).

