Axillary ultrasound, the most used imaging modality for nodal assessment, is an unreliable staging modality for BC patients with a low nodal metastatic burden; its negative predictive value (60% to 90%) is not reassuring [5,6,7,8,9]. Different rates of sensitivity and specificity of axillary ultrasound are reported in the literature, ranging from 26% to 94% and from 53% to 98%, respectively [7,8,9,10,11]. Thus, for most BC patients presenting with a clinically and radiologically node-negative axilla at diagnosis, in the quest to reliably stage the axilla, the surgical sentinel-node procedure is routinely used for staging [12]. However, for BC patients aged >70 years with hormone-receptor-positive and human epidermal growth factor receptor 2 (HER2)-negative conditions, sentinel-lymph-node surgery is optional if the patient receives adjuvant endocrine therapy according to ASCO guidelines [12]. However, these guidelines are not implemented in Sweden, and the surgical management of the axilla is the same, independent of age at diagnosis and molecular subtype. In the majority (~80%) of early BC patients undergoing sentinel-node surgery, the procedure identifies only healthy lymph nodes with no metastatic tumor deposits [3,4]. For these patients, the invasive surgical procedure is diagnostic but not therapeutic.

Although there are many benefits of the minor surgical sentinel-node procedure compared to axillary dissection, sentinel-node surgery is associated with short- and long-term side effects. Most importantly, immediate postoperative swelling, paresthesia, arm lymphedema, and self-reported symptoms of arm swelling are documented complications of the sentinel-node procedure [13,14]. In addition, the procedure is time-consuming and requires financial healthcare resources.

We previously developed and published a decision-making tool, the noninvasive lymph node staging (NILS) prediction model, for the prediction of benign lymph nodes in primary BC [15]. The NILS prediction model, which is an artificial neural network (ANN) model, was developed using retrospectively collected variables (including patients, *n* = 800). The NILS prediction model includes ten top-ranked risk variables for nodal status (please refer to Section 2.1), including hormone receptor status but excluding molecular subtype. The aim of this study is to retrospectively validate the NILS prediction model in one temporal and one geographical cohort.

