### 2.6. Power Calculation and Statistical Plan

We estimated that the sample size would be *n* = 300 study participants, and although each validation cohort will be assessed separately, the total number would be *n* = 600. Due to practical reasons (shortage of qualified research personnel at one of the study sites), we will include *n* = 400 from the temporal cohort and *n* = 200 from the geographical cohort. The area under the curve (AUC) for the original prediction model was 0.74 in a development cohort, where two-thirds of the patients were node-negative [15]. Assuming the same proportion of N0 and the same discrimination for future patients, the inclusion of 300 patients is sufficient to obtain 90% probability of reaching an AUC of at least 0.70 in this validation study. This calculation was based on the asymptotic normality of the AUC estimate and simulations that determined the relationship between the sample size and standard error of the AUC estimate. The performance of the ANN decision tool upon validation will be assessed in terms of discrimination (AUC) and calibration (comparison of the observed and predicted event rates of benign axillary nodal status, Hosmer–Lemeshow test). Separate analyses of patients undergoing breast-conserving surgery and mastectomy will be performed. No interim analyses will be performed. Patients will be screened for eligibility according to specified inclusion and exclusion criteria and subsequently included if all criteria are fulfilled. Study participants for whom mandatory variables for the NILS protocol are missing, i.e., variables that the ANN model cannot predict, will be excluded.

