## 3. Discussion

We present a study protocol for the validation of an ANN model for the prediction of healthy lymph nodes in patients with early BC with clinically and ultrasound-diagnosed node-negative disease (ISRCTN14341750).

The sentinel-node-biopsy technique has a well-established threshold for a false-negative rate of 10% [19,20], and we consider this threshold acceptable in the presented predictive setting of our ANN model. The Swedish Institute of Health Economy conducted a technical report concluding that our prediction model will be cost-saving if its accuracy is consistent with that reported in our previous publication [15].

The optimal management of the axilla in patients with BC is under discussion in clinical and scientific societies. While a normal standard axillary ultrasound examination is insufficient to rule out axillary nodal metastasis [21], improved functional imaging, such as magnetic resonance imaging (MRI) or positron emission tomography/MRI, in preoperative settings provides the same performance as sentinel-node biopsy for excluding axillary lymph node metastases [22,23,24,25,26]. Although these imaging modalities have higher accuracy when determining axillary status, their availability in preoperative settings is not universal, and the presented data are hitherto based on a limited series (Bruckmann et al., *n* = 104; Botsikas et al., *n* = 80; in a review article by Kuijs et al., the largest included study was *n* = 505).

Two randomized controlled trials are investigating the possibility of abstaining from sentinel-node biopsy in patients with BC stage T1 undergoing breast-conserving surgery: the SOUND trial (ClinicalTrials.gov identifier: NCT02167490), which has an estimated data completion date in Q4 2021, and the INSEMA trial, which includes patients with T1–T2 tumors (ClinicalTrials.gov identifier: NCT02466737) and has an estimated data completion date in Q4 2024. The results from these trials will provide qualitative insights into the oncological safety of omitting sentinel-node surgery.

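### The 10% false-negative limit is borrowed from sentinel-node biopsy but measured against sentinel-node pathology, so the two figures are not equivalent; the study, sized on the AUC, also estimates this rate imprecisely

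*Protocol article*

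**What the plan says.** Section 2.9.2 fixes the criterion: "The secondary endpoint is defined as a false-negative rate of a maximum of 10% for the prediction of N0 vs. N" (N+ in full). The same sentence gives the comparator: "compared to the histopathological assessment of excised sentinel lymph node(s"). The article names no interval, bound or confidence level for this rate.

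The Discussion (section 3) notes that the sentinel-node technique has an established 10% false-negative threshold and adds: "we consider this threshold acceptable in the presented predictive setting of our ANN model".

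Section 2.6 sizes the study on the AUC: 300 patients for a 90% probability of an AUC of at least 0.70. It adds "although each validation cohort will be assessed separately". Because of staffing, "we will include *n* = 400 from the temporal cohort and *n* = 200 from the geographical cohort".

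Two figures bear on the number of node-positive patients. Section 2.6 describes a development cohort "where two-thirds of the patients were node-negative". The Introduction says: "In the majority (~80%) of early BC patients undergoing sentinel-node surgery, the procedure identifies only healthy lymph nodes".

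Section 3.1 describes the intended use: the tool would support shared decisions on omitting sentinel-node biopsy in patients predicted to be node-negative. Section 2.8 excludes patients with upfront axillary dissection.

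**The concern.** There are two separate problems.

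The first is the benchmark. A false-negative rate for sentinel-node biopsy counts metastatic axillae that the biopsy fails to find. The model's rate counts patients with a positive sentinel node whom the model calls N0. A patient whose metastasis the biopsy misses enters this study as N0 and cannot count as a model error. The 10% accepted for one quantity therefore does not carry over to the other. Meeting the limit would not put the model level with biopsy.

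The second is precision. The denominator of the rate is node-positive patients only, a minority of each cohort, and the sample size was not chosen with this rate in mind. In the smaller cohort, an observed rate at or just under 10% is compatible with a true rate well above it.

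At stake is what may be said afterwards. This is the stated numerical criterion that counts node-positive patients called node-negative, and the article links satisfactory performance to use in decisions on omitting biopsy.

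**Working it through.** **Inputs from the article.** Limit 10% (2.9.2); cohorts of 400 and 200 (2.6); N+ share 1/3 (2.6) or about 20% (Introduction); AUC 0.74, target 0.70, n = 300 (2.6).

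**Assumptions, not in the article.** A true model false-negative rate (FNR) of 15% or 12%; a biopsy FNR of 0–10%; the point estimate decides; the cut point is fixed beforehand.

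**1. The plan's own figure.** P(observed AUC ≥ 0.70) = Φ((0.74 − 0.70)/SE). With 100 N+ and 200 N0, the Hanley–McNeil SE is 0.0319 or 0.0285, depending on which group is treated as the event. This gives 89.5% or 92.0%. A binormal simulation gives 90.7%. The stated 90% is reproduced, but it says nothing about the FNR.

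**2. Node-positive patients.**
- Geographical: 200 × 0.20 = 40; 200/3 ≈ 67.
- Temporal: 400 × 0.20 = 80; 400/3 ≈ 133.
- Both together: 600 × 0.20 = 120; 600/3 = 200.

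**3. Interval when the criterion is just met.** With m node-positive patients, the largest passing count is the integer part of 0.10 × m. Exact (Clopper–Pearson) 95% limits:

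| Cohort | Misses / N+ | Observed | 95% CI |
|---|---|---|---|
| Geographical | 4/40 | 10.0% | 2.8–23.7% |
| Geographical | 6/67 | 9.0% | 3.4–18.5% |
| Temporal | 8/80 | 10.0% | 4.4–18.8% |
| Temporal | 13/133 | 9.8% | 5.3–16.1% |
| Pooled | 12/120 | 10.0% | 5.3–16.8% |
| Pooled | 20/200 | 10.0% | 6.2–15.0% |

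**4. Chance of passing if the point estimate decides.** P(X ≤ integer part of 0.10 × m), with X binomial(m, true FNR):

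| N+ | True FNR 15% | True FNR 12% |
|---|---|---|
| 40 | 26.3% | 46.7% |
| 67 | 10.7% | 29.3% |
| 80 | 13.4% | 36.7% |
| 133 | 5.3% | 26.2% |
| 120 (pooled) | 7.5% | 30.6% |
| 200 (pooled) | 2.5% | 22.7% |

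Over all m from 40 to 67, the 15% column runs from 10.6% to 26.3%. If the number of N+ among 200 patients is itself random, it is 20.1% (20% N+) or 12.9% (1/3 N+).

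**5. Compounding.** Under the intended use, a metastasis is found only if the biopsy would detect it and the model does not call the patient N0. The model's FNR is already conditional on a positive sentinel node, so the two detection probabilities multiply without an independence assumption:

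overall miss rate = 1 − (1 − FNR of model) × (1 − FNR of biopsy)

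With the model at 10%:
- biopsy 0%: 1 − 0.90 × 1.00 = 10%
- biopsy 5%: 1 − 0.90 × 0.95 = 14.5%
- biopsy 10%: 1 − 0.90 × 0.90 = 19%

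Only if biopsy missed nothing would the overall figure be 10%.

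**6. What a strict upper-limit rule would demand.** A two-sided 95% upper limit of at most 10% allows 0/40, 1/67, 5/120 or 11/200 misses. A model with a true FNR of 5% would meet this 13%, 15%, 44% or 70% of the time. For 80% at that true rate, about 231 N+ patients are needed, more than the 120 to 200 expected in the whole study.

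**The case against.** The article is a condensed protocol. How a secondary threshold is judged (interval, confidence level, per cohort or pooled) is commonly left to a full protocol or SAP that is not shown. This stands: the absence of an interval rule is not itself an error. The article also does not say that the point estimate decides, and the phrase "each validation cohort will be assessed separately" sits in the sample-size paragraph and is not tied to the FNR. The pass rates in step 4 are therefore conditional.

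A reader might infer that a poor model would often pass. The figures do not support that. At an assumed true rate of 15%, the model fails in 74–89% of studies in the geographical cohort, and in 92.5–97.5% if the cohorts are pooled.

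A reader might also infer that the article claims the same overall miss rate as biopsy, or that 19% is the expected rate. It claims only that the threshold is acceptable for the model. It reports no achieved biopsy rate, so 19% is the value at the ceiling and belongs in a range. Nor is the FNR the only measure of performance: calibration is assessed too, and the Discussion looks to randomised trials for the oncological safety of omission.

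The direction of a false negative (N+ called N0) is clear enough from section 2.9.2 and the biopsy benchmark, although section 2.6 treats benign status as the event.

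Finally, requiring the upper limit to lie below 10% would fail most good models at this sample size (step 6). That objection stands too, and such a rule is not proposed.

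**Conclusion.** The concern holds in two parts. The benchmark argument rests on the article's own text, and no analysis detail elsewhere would repair it. The limit is taken from biopsy, the reference standard is biopsy pathology, and the two 10% figures measure different things. With the model at its limit, the overall miss rate lies between 10% and 19% for assumed biopsy rates of 0–10%.

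The precision argument is also sound, but moderate in size. With 40 to 67 node-positive patients in the geographical cohort, a just-met criterion leaves rates up to 18.5–23.7% inside the 95% interval. The upper limit exceeds twice the threshold at 40 node-positive patients but not at 67. The chance of 11–26% that a model with a true rate of 15% passes depends on that assumed rate, on a point-estimate decision and on a cut point fixed in advance. Exclusions for missing mandatory variables, if not replaced, could lower the node-positive count further.

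This should be addressed before results are reported. It does not invalidate the design.

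**What to change.** - Define the FNR as pN+ patients predicted N0, divided by all pN+ patients, at the web tool's existing cut point (shown in Figure 2), unchanged by the validation data.
- Report it with an exact 95% interval in each cohort and, as support, pooled over both. This keeps the separate assessment in section 2.6.
- Where the upper limit exceeds 10%, say that a rate above 10% is not excluded. Do not make the upper limit a pass/fail rule.
- State in section 2.9.2 and the Discussion that the FNR is relative to sentinel-node pathology. Next to the 10% benchmark, give 1 − (1 − FNR of model)(1 − FNR of biopsy) over a range of assumed biopsy rates.

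The cost is some wording and a routine calculation, with no new data. The downside is a less favourable claim when the interval is wide, which is likely in the geographical cohort.

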### 2.10. Data Analysis

For secure and trackable data entry, REDCap [18] with audit trail is being used. A comprehensive data-management plan was developed. Only the principal investigator and responsible researchers will be granted access to the final dataset. Personal information of enrolled patients will be collected, shared, and maintained with a high level of caution and according to local and national regulations to protect confidentiality before, during, and after the trial. All collected data will be stored in an encrypted database (REDCap), which will remain in the custody of the principal investigator.

A risk analysis was conducted, and a detailed plan for data monitoring (conducted by an external researcher) was established (Supplementary Material S1).

## 3. Discussion

We present a study protocol for the validation of an ANN model for the prediction of healthy lymph nodes in patients with early BC with clinically and ultrasound-diagnosed node-negative disease (ISRCTN14341750).

The sentinel-node-biopsy technique has a well-established threshold for a false-negative rate of 10% [19,20], and we consider this threshold acceptable in the presented predictive setting of our ANN model. The Swedish Institute of Health Economy conducted a technical report concluding that our prediction model will be cost-saving if its accuracy is consistent with that reported in our previous publication [15].

The optimal management of the axilla in patients with BC is under discussion in clinical and scientific societies. While a normal standard axillary ultrasound examination is insufficient to rule out axillary nodal metastasis [21], improved functional imaging, such as magnetic resonance imaging (MRI) or positron emission tomography/MRI, in preoperative settings provides the same performance as sentinel-node biopsy for excluding axillary lymph node metastases [22,23,24,25,26]. Although these imaging modalities have higher accuracy when determining axillary status, their availability in preoperative settings is not universal, and the presented data are hitherto based on a limited series (Bruckmann et al., *n* = 104; Botsikas et al., *n* = 80; in a review article by Kuijs et al., the largest included study was *n* = 505).

Two randomized controlled trials are investigating the possibility of abstaining from sentinel-node biopsy in patients with BC stage T1 undergoing breast-conserving surgery: the SOUND trial (ClinicalTrials.gov identifier: NCT02167490), which has an estimated data completion date in Q4 2021, and the INSEMA trial, which includes patients with T1–T2 tumors (ClinicalTrials.gov identifier: NCT02466737) and has an estimated data completion date in Q4 2024. The results from these trials will provide qualitative insights into the oncological safety of omitting sentinel-node surgery.

Data supporting the impact of the pathological staging of the axilla on adjuvant systemic treatment recommendations are limited to luminal A-like tumors; thus, the need to detect axillary lymph node metastasis in early BC is of less importance. In a study by van Roozendaal et al., the decision to recommend adjuvant systemic treatment changed in only 1% of the patients due to a pathological lymph node status when using Adjuvant! Online [27], and a report of *n* = 1001 patients included in the INSEMA trial showed that tumor biological parameters alone guided systemic treatment decisions in 99% of the patients [4].

In the NILS prediction model, hormonal status and Ki67, but not molecular subtype, are included. In the initial development of the model, presented by Dihge et al., a strong correlation was found between grade and Ki67 [15]. Grade was excluded and Ki67 was retained in the final model to minimize the risk of collinearity [15]. In addition, HER2 was not identified as a predictor of nodal status and was not included.

Many nomograms and ANN models have been developed for predicting nodal metastasis, or the lack thereof, with [28,29,30,31,32,33,34,35,36] or without imaging [37,38,39,40]. The discrimination of clinical nomograms including clinicopathological data only is equivalent to the predictions made by the NILS prediction model (area under the curve (AUC) 0.73–0.75 [39,40]), whereas those incorporating radiomic features present an AUC slightly above 0.90 [30,31,32,34]. However, the ANN model that this study aims to validate is a promising tool in the clinic because the input variables are routinely available, no extra imaging besides clinical work-up (i.e., mammography and axillary ultrasound) is necessary, and the web interface is user-friendly.

### 3.1. Significance

Internationally, there are numerous artificial intelligence projects involving the noninvasive identification of N0 BC. The NILS protocol uses easily accessible clinicopathological variables, including mammography data, and, in contrast to many other algorithms, does not require medical imaging data for machine learning analysis. We present a robust validation study of the NILS prediction model based on two external cohorts. If the accuracy and discrimination reach a satisfactory level, our prediction tool (the NILS protocol) can be implemented and would assist medical professionals and BC patients in shared decision making on omitting sentinel-node biopsy in patients predicted to be node-negative. In the future, the use of the NILS protocol may save healthcare resources and reduce both costs and unbeneficial side effects. In addition, the NILS prediction model and our presented validation study may prompt future studies of nodal metastases of malignancies in other organs; thus, it may have implications beyond BC. 

### 3.2. Current Status

Clinicopathological data are being retrieved from electronic medical charts and pathology reports along with the output from the web application for the ANN. Specially trained research nurses and research administrators with many years of experience in data management are responsible for data entry. Data entry began in Q3 2021 and will be completed in Q1 2022.

## Figures and Tables

**Figure 1 diagnostics-12-00582-f001:**
[figure not shown]
Schedule of enrollment, data collections, and monitoring. * Waived by the ethics committee. ** For a more extensive monitoring schedule for these critical variables, please refer to Supplementary Material S1.

**Figure 2 diagnostics-12-00582-f002:**
[figure not shown]
Screenshots from the web interface of the nodal status classifier. (**a**) Data input resulting in an estimated probability of healthy lymph nodes below the cut point, (**b**) data input resulting in an estimated probability of healthy lymph nodes above the cut point.

## Data Availability

This is not applicable to the study protocol. Following the enrollment of participants, the raw datasets are kept with the corresponding author and available upon reasonable request due to restrictions, such as privacy and ethical restrictions. The data are not publicly available because of these restrictions. The study results will be made public through a peer-reviewed publication in an international journal. The full protocol, participant-level dataset, and statistical code will not be publicly available because of privacy and ethical restrictions.
